### Control Group

Physicians not participating in the program serve as controls, either among the 8 participating regional Associations of Statutory Health Insurance Physicians (control group 1) or among the remaining associations not participating in RESIST (control group 2).

### Outcomes

The primary outcome measure is the overall antibiotic prescription rate of all patients insured with a German statutory health insurance before and after the provision of online courses. Secondary outcomes are (a) the antibiotic prescription rate for ARTI in patients aged ≥ 1 year before and after the intervention; (b) the antibiotic prescription rate based on different types of ARTI (eg, otitis media, bronchitis, pneumonia; see Table 1) before and after the intervention in patients aged ≥ 1 year; and (c) quality of antibiotic prescribing for ARTI measured by internationally accredited quality indicators of the European Surveillance of Antimicrobial Consumption Project (ESAC) [15], again before and after the intervention.

**Table 1 table1:** International Classification of Diseases codes relevant for diagnosing acute respiratory tract infection.

Code	Diagnosis
J00	Acute nasopharyngitis (common cold)
J01	Acute sinusitis
J02	Acute pharyngitis
J03	Acute tonsillitis
J04	Acute laryngitis and tracheitis
J06	Acute upper respiratory infections of multiple and unspecified site
J09	Influenza due to identified zoonotic or pandemic influenza virus
J10	Influenza due to identified seasonal influenza virus
J11	Influenza, virus not identified
J12	Viral pneumonia, not elsewhere classified
J13	Pneumonia due to *Streptococcus pneumoniae*
J14	Pneumonia due to *Haemophilus influenzae*
J15	Bacterial pneumonia, not elsewhere classified
J16	Pneumonia due to other infectious organisms, not elsewhere classified
J17	Pneumonia in diseases classified elsewhere
J18	Pneumonia, organism unspecified
J20	Acute bronchitis
J21	Acute bronchiolitis
J22	Unspecified acute lower respiratory infection
J40	Bronchitis, not specified as acute or chronic
H65	Nonsuppurative otitis media
H66	Suppurative and unspecified otitis media

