### Intervention

The intervention is based on an online training course consisting of three modules. Each module can be completed within approximately 1 hour. Module 1 focuses on patient-centered doctor-patient communication, and points to typical communicative situations when treating patients with ARTI. Within the module, physicians are encouraged to reflect upon these situations and to question perceived pressure to prescribe antibiotics. Modules 2 and 3 deal with rational antibiotic use in the case of upper and lower respiratory tract infections. After passing the Continued Medical Education–accredited course, physicians receive posters and brochures on rational antibiotic use to display them in their practices or to use them during consultations. Physicians successfully completing the course receive a one-time allowance. In addition, physicians receive further reimbursement for up to 20 patients with ARTI per quarter, which they document as treated according to the strategies adopted after participating in the online training. In addition, participating physicians receive a feedback report on aggregated data on regional antibiotic prescribing patterns. Figures are compared between intervention and control groups. See Multimedia Appendix 1 for more details on each component and module of the intervention [14].

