## Discussion

With up to 3000 physicians participating in the program, RESIST is among the largest real-world interventions aiming at reducing inadequate antibiotic prescribing for ARTI in primary care. Long-term follow up of up to 21 months will allow for investigating the sustainability of the intervention.

As RESIST utilizes an open-label nonrandomized evaluation concept, potential bias has to be carefully addressed. Bias may arise from the fact that physicians most interested in reducing inadequate antibiotic prescriptions are also likely to be those most motivated to take part in RESIST. To counteract this, we make use of an attractive incentivization and reimbursement scheme. In addition, the inclusion of comparable practices not participating in the program (both among participating regions and among those not participating in RESIST) allows for control of this potential source of bias.

We will also minimize bias due to changed coding. For example, a clinically identical patient treated with antibiotics might be coded with lower respiratory tract infection initially but with pneumonia after the intervention, leading to an overestimation of the interventional effect. By measuring the overall antibiotic prescribing rate of antibiotics without regard to any specific disease as the primary outcome measure, we can exclude bias due to coding phenomena.

Last but not least, the RESIST program joins the ranks of other current initiatives to reduce inadequate antibiotic prescribing. Thus, contamination effects between the projects are possible. However, by including a high number of physicians and practices among half of all German states, we believe to be able to address this potential source of bias adequately.

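### The answer to LRTI-to-pneumonia recoding protects the primary outcome but leaves the lower-tract rates in secondary outcome (b) exposed

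*Protocol article*

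**What the plan says.** The Discussion of the protocol article sets a general aim, "We will also minimize bias due to changed coding", and gives one example. It concerns a treated patient whose clinical picture has not changed and who, in its words, "might be coded with lower respiratory tract infection initially but with pneumonia after the intervention, leading to an overestimation of the interventional effect". The remedy offered is to measure overall prescribing "without regard to any specific disease as the primary outcome measure, we can exclude bias due to coding phenomena".

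The Outcomes section lists three secondary outcomes that rest on coded diagnoses:

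- the pooled ARTI rate, outcome (a);
- outcome (b), "the antibiotic prescription rate based on different types of ARTI (eg, otitis media, bronchitis, pneumonia; see Table 1) before and after the intervention";
- outcome (c), "quality of antibiotic prescribing for ARTI measured by internationally accredited quality indicators".

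Table 1 defines ARTI by 22 codes. They include pneumonia (J12 to J18) and the other lower-tract codes (J20 to J22 and J40).

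Under Statistical Methods, the secondary outcomes and the indicators are analysed with the same kind of model as the primary outcome. That is a negative binomial regression with the number of patients as offset, adjusted for the pre-intervention prescription rate, region, specialization, and the sex, age and insurance mix. No term or check concerns changes in coding.

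The Intervention section states that "Modules 2 and 3 deal with rational antibiotic use in the case of upper and lower respiratory tract infections". Only participating physicians take these modules.

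**The concern.** The example and the remedy do not meet. Recoding within Table 1 never reaches the primary outcome, which ignores diagnosis. It can bias a rate only where lower respiratory infection and pneumonia are counted separately, and outcome (b) does this. When a treated patient moves from a bronchitis code to a pneumonia code, one treated patient leaves both the numerator and the denominator of the bronchitis rate. That rate falls although prescribing has not changed.

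The control group need not cancel the shift, because the modules on these diagnoses are taken by the intervention group only and the example itself places the recoding after the intervention. Adjustment for the pre-intervention rate cannot remove a change that starts later in one arm, and the other planned covariates do not measure coding.

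What is at stake is the reading of (b), which is meant to show in which infections prescribing changed. A reader who takes the Discussion's closing words, "we can exclude bias due to coding phenomena", as covering all outcomes could accept a coding artefact in bronchitis as a real reduction.

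**Working it through.** **Inputs**

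- Expected secondary effect: 30.5% versus 27.5%, power 80%, two-sided 5%, ICC 0.08, 127 ARTI patients per practice (Sample Size).
- Code groups: Table 1 (Outcomes).
- Prescription rate within LRTI or bronchitis: not given. Assumed 30.5%, with a range of 20% to 60%.
- Each recoded patient is treated, as in the Discussion's example. One prescription per treated patient is assumed.

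**1. The plan's own figure.** With pooled variance, n per arm = [1.96·√(2·0.29·0.71) + 0.8416·√(0.305·0.695 + 0.275·0.725)]² / 0.03² ≈ 3,590.1, or 3,591 rounded up (stated 3,590). The design effect is 1 + 126·0.08 = 11.08. Then 3,590·11.08 = 39,777 patients, or 313.2 practices. The stated 39,751 is 313·127. The figures reproduce, and they confirm that the 3-point expectation belongs to the pooled ARTI rate.

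**2. Effect of recoding on a single type.** Let p be the rate in the LRTI stratum and x the share of its patients, all treated, who are recoded to pneumonia. The new rate is (p − x)/(1 − x). A fall to t therefore needs x = (p − t)/(1 − t).

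- p = 30.5%, x = 2%: 28.5/98 = 29.1%.
- p = 30.5%, t = 27.5%: x = 0.03/0.725 = 4.14% of LRTI patients, which is 4.14/30.5 = 13.6% of the treated ones.

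On the scale of the planned model, the second line is a rate ratio of 27.5/30.5 = 0.90 without any change in prescribing.

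**3. Sensitivity to the assumed base rate, for a 3-point fall**

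| Assumed LRTI rate | Share of LRTI patients recoded | Share of treated LRTI patients |
|---|---|---|
| 20% | 0.03/0.83 = 3.6% | 18.1% |
| 30.5% | 0.03/0.725 = 4.1% | 13.6% |
| 40% | 0.03/0.63 = 4.8% | 11.9% |
| 50% | 0.03/0.53 = 5.7% | 11.3% |
| 60% | 0.03/0.43 = 7.0% | 11.6% |

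**4. Where the shift shows and where it does not.** Take 1,000 ARTI patients and assume 300 with LRTI at 30.5% (91.5 treated) and 20 with pneumonia at 80% (16 treated). Recoding 4.14% of the LRTI patients moves 12.41.

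- LRTI: (91.5 − 12.41)/(300 − 12.41) = 79.09/287.59 = 27.5%.
- Pneumonia: (16 + 12.41)/(20 + 12.41) = 28.41/32.41 = 87.7%, up from 80%. Its share of ARTI patients rises from 2.0% to 3.2%.
- LRTI and pneumonia combined: 107.5/320 = 33.6% before and after.
- Pooled ARTI rate and overall rate: numerator and denominator unchanged, so the change is zero.

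The combined rate and the table of code shares thus separate recoding from a real change, which the bronchitis rate alone cannot do.

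**The case against.** The strongest reply has four parts.

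First, the exclusion sentence is argued through the primary outcome, and the paragraph's general aim is only to minimize coding bias. This stands. The sentence is loose at its end, but it makes no explicit claim about (b) or (c). A reader might infer that the protocol declares every outcome free of coding bias, and its grammar does not support that.

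Second, a reader might infer that recoding alone could produce the whole expected effect of the trial's secondary outcome. It could not. The fall from 30.5% to 27.5% is stated for the pooled ARTI rate, on which this recoding has no effect. No fall is stated for any single type, so 3 points serves here only as a measure of size.

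Third, not all of (b) is exposed. The upper-tract, influenza and otitis codes, 11 of the 22 in Table 1, are untouched by a move from LRTI to pneumonia. For (c), the article does not define the individual indicators, so their exposure cannot be shown from it. Both limits stand.

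Fourth, the planned outcomes already offer cross-checks. Recoding that lowers the bronchitis rate would tend to raise the pneumonia rate and would leave the pooled rate still. This is true in part. But the pooled rate also contains upper-tract infections and otitis, so it is a blunt check on the lower tract, and nothing in the article says that the results will be read together.

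The grouping of codes could be left to an analysis plan. The mismatch between the named bias and the remedy offered is in the article itself.

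**Conclusion.** The point holds for the lower-tract, type-specific rates in (b). A bias that the protocol names itself is answered only through an outcome it cannot reach, and the outcomes it can reach have no stated safeguard.

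At an assumed LRTI rate of 30.5%, recoding about 4.1% of LRTI patients imitates a 3-point fall. For base rates of 20% to 60% the share is 3.6% to 7.0% of LRTI patients, or 11% to 18% of the treated ones. This assumes that every recoded patient is treated and that the shift occurs in the intervention group only. The document makes both plausible but measures neither, and whether recoding of this extent occurs is unknown.

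The primary outcome, the pooled ARTI rate, the sample size and the confirmatory comparison with control group 1 are unaffected by this mechanism.

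**What to change.** - In (b), add a combined lower-tract rate (J12 to J18, J20 to J22, J40), analysed with the same model, alongside the bronchitis and pneumonia rates.
- Tabulate the share of ARTI patients in each code group by arm and period, and interpret a change in bronchitis alone or pneumonia alone together with this table and the combined rate.
- In the Discussion, limit the exclusion of coding bias to the primary outcome. State that type-specific rates, and any indicator with a diagnosis-specific denominator, remain sensitive to changed coding.

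The cost is one extra grouping, one table and a sentence. Data Collection already lists grouped and individual ARTI diagnoses, so no new data item is needed. The combined group is clinically less specific, but the single-type rates stay in the report.

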### Sample Size

With respect to the primary outcome, a reduction of the physicians’ overall antibiotic prescription rate by 1% is assumed for RESIST (from 33.8% in the control group 1 to 32.8% in the intervention group). Without consideration of cluster effects, 2 × 34,865 patients are needed to show this effect with a power of 80% and a type I error of 5% (two-sided). Assuming an intracluster correlation (ICC) of 8% [16] and an average cluster size of 160 patients per practice, a design effect of 13.72 is determined. Overall, the sample size increases to 2 × 478,400 patients (956,800 patients in total). Thus, 2 × 2990 practices (5980 in total) are needed for the evaluation.

For the secondary outcome, a reduction of 3% in the physicians’ antibiotic prescription rate for ARTI is expected (from 30.5% in the control group 1 to 27.5% in the intervention group). Assuming a power of 80% and a type I error of 5% (two-sided), 2 × 3590 patients are required. With an ICC of 8% [16] and an average cluster size of 127 patients (diagnosed with ARTI) per practice, the sample size increases to 2 × 39,751 patients (79,502 patients in total). Hence, 2 × 313 practices are needed (626 practices in total). The sample size necessary to investigate the effect of the intervention on the primary outcome will be adequate to investigate its effect on the secondary outcome as well.

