**Conclusions:**

With approximately 3000 physicians participating in the program, RESIST is among the largest real-world interventions aiming at reducing inadequate antibiotic prescribing for ARTI in primary care. Long-term follow up of up to 21 months will allow for investigating the sustainability of the intervention.

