### Recruitment

Recruitment of participating physicians is undertaken in 8 German federal states and regions (Bavaria, Baden-Wuerttemberg, Lower Saxony, North Rhine, Westphalia-Lippe, Brandenburg, Mecklenburg-Western Pomerania, and Saarland), assisted by the respective regional Association of Statutory Health Insurance Physicians. General practitioners, primary care pediatricians, and practice-based otorhinolaryngologists can enroll in the RESIST program on a voluntary “first-come, first-served” basis. The maximum number of participating physicians per region is related to the size of the regional association. In total, we aim to include up to 3000 physicians in the program.

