### Data Collection, Completeness, and Quality

The trial is based on pseudonymized routine data provided by the Zi. The dataset is based on aggregated practice data. Information collected includes: age groups and sex of patients, ARTI diagnoses (grouped and individual diagnoses), antibiotic prescriptions, group affiliation of the physician (intervention vs control), region, level of urbanization, and type of medical insurance of the patient.

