## Results

RESIST is publicly funded by the Innovations funds of the Federal Joint Committee (G-BA) in Germany (funding code: 01NVF16005) and was approved in December 2016.

Recruitment of physicians is completed. A total of 2460 physicians participated in the intervention. Data analysis started in February 2020.

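### The 80% power is stated for two equal groups of 2990 practices, but the intervention group can have at most 2460 and the controls are not selected 1:1, so the power of the comparison actually described is not given

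*Protocol article*

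**What the plan says.** The Sample Size section assumes a fall in the overall antibiotic prescription rate "from 33.8% in the control group 1 to 32.8% in the intervention group". For 80% power at a two-sided 5% level it states that, before clustering, "2 × 34,865 patients are needed". An intracluster correlation of 8% and 160 patients per practice give a design effect of 13.72. The section concludes that 2 × "2990 practices (5980 in total) are needed for the evaluation".

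The Recruitment section counts physicians: "In total, we aim to include up to 3000 physicians in the program". The Results section reports that recruitment is complete: "A total of 2460 physicians participated in the intervention". The abstract gives the same 2460 in its Results, yet its Conclusions read "With approximately 3000 physicians participating in the program, RESIST is among the largest real-world interventions". The Discussion also still refers to a maximum of 3000.

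The Study Design, Participants and Control Group sections define controls as physicians who do not take part, and those in the eight participating regions form control group 1. None of these sections describes sampling, matching or a cap that would produce equal groups. Statistical Methods makes the practice the sampling unit and treats the comparison with control group 1 as confirmatory.

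**The concern.** The size calculation and the comparison differ in three respects.

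- **Unit.** The requirement is in practices and recruitment is in physicians. Nothing converts one into the other. Even a full 3000 physicians would yield 2990 practices only if almost no participants shared a practice, so the margin was nearly nil from the outset.
- **Number.** Recruitment ended at 2460 physicians, and the calculation is not revisited although the article already reports that count.
- **Allocation.** The calculation assumes equal groups, but the control definition does not produce them.

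The stated 80% is therefore not the power of the confirmatory comparison. A reader who judges the planned sensitivity of the trial by that figure, particularly after a null result, would be using a number that belongs to another design.

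**Working it through.** **Inputs (Sample Size section):** rates 0.338 and 0.328; two-sided 5% level; 80% power; intracluster correlation 0.08; 160 patients per practice. **From Results:** 2460 participating physicians. **Not in the document:** the number of intervention practices and the number of control group 1 practices. Values for these are assumptions and are shown as a range.

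**1. Reproducing the plan's figure.**

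- The two-proportion formula with pooled variance under the null gives 34,865.3 patients per group, which agrees with the stated 34,865.
- Design effect: 1 + (160 − 1) × 0.08 = 13.72.
- Patients per group: 34,865 × 13.72 = 478,348.
- Practices per group: 478,348 / 160 = 2989.7, rounded up to 2990 (2990 × 160 = 478,400, as stated).

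The arithmetic is right for a 1:1 design.

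**2. Upper limit on intervention practices.** 2460 physicians cannot work in more than 2460 practices if each is counted once. 2460 / 2990 = 0.82.

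**3. Power for other sizes.** With k intervention practices and r control practices for each of them:

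- SE = √[(13.72 / 160) × (0.328 × 0.672 / k + 0.338 × 0.662 / (r·k))]
- power = Φ(0.01 / SE − 1.96)

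For k = 2460:

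- r = 1: SE = 0.003935, 0.01 / SE = 2.541, power = Φ(0.581) = 72%.
- r = 1.56 (about 3840 controls): SE = 0.003561, 0.01 / SE = 2.808, power = Φ(0.848) = 80%.
- r = 2: SE = 0.003403, 0.01 / SE = 2.938, power = Φ(0.978) = 84%.
- r = 5: SE = 0.003040, 0.01 / SE = 3.289, power = Φ(1.329) = 91%.

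| Intervention practices | 1:1 | 1:2 | 1:3 | 1:5 |
|---|---|---|---|---|
| 2990 (plan) | 80% | 90% | 93% | 95% |
| 2460 (maximum possible) | 72% | 84% | 88% | 91% |
| 2000 (assumed) | 63% | 75% | 80% | 84% |
| 1640 (assumed, 1.5 physicians per practice) | 55% | 67% | 72% | 77% |

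Pooling the variance under the null changes no entry by more than about half a percentage point; for example, 1640 practices at 1:5 give 76% instead of 77%.

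**4. Floor.** As r grows without limit, the control term vanishes. Then 80% power needs k = (1.960 + 0.842)² × 0.2204 × (13.72 / 160) / 0.01², which is about 1480, or about 1500 with the pooled form. Below roughly 1500 intervention practices, no number of controls reaches 80% on these inputs.

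**The case against.** The case on the other side is substantial.

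- **A shortfall is not a planning error.** The recruitment target is worded as a ceiling, the achieved 2460 is reported openly, and a prospective calculation properly records what was assumed at the time. This stands. It does not cover the near-zero margin between 2990 practices and 3000 physicians, or the equal-group assumption, both of which were there at the design stage.
- **Extra controls can make up the difference.** With 2460 intervention practices, about 3840 controls restore 80%. If control group 1 takes in every non-participant in eight regions, it may well be that large. This stands too, but the article does not give the number.
- **The planned model adjusts for the baseline prescription rate** and for case mix, which the calculation ignores. If the covariates removed 18% of the variance (an assumption; the article gives no figure), 2460 against 2460 would already give 80%. The unadjusted figures above may therefore be pessimistic.
- **The result will be read from the rate ratio and its confidence interval**, not from planned power. This is true, and it limits the consequence, but it does not make the stated figure apply to this comparison.

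A reader might go further and infer that the trial is underpowered. The document does not support this, because the figures run from well below to well above 80% depending on two numbers that it does not give. A reader might also infer, from "The dataset is based on aggregated practice data" together with group affiliation recorded per physician, that a practice with both trained and untrained physicians counts in both groups and dilutes the contrast. No section says how such practices are classified. The rule is a detail that a condensed article may leave to the full protocol or analysis plan. It is a question to ask, not a demonstrated error.

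**Conclusion.** The point holds in a limited form. The calculation is correct for 2 × 2990 practices, but the intervention group falls at least 18% short of that number and control group 1 is not formed at 1:1. The stated size is not met, and the stated 80% is not the power of the confirmatory comparison. At the most favourable count of one participating physician per practice, power runs from about 72% at 1:1 to about 91% at 1:5, and it is lower with fewer practices. These figures rest on the plan's own rates, intracluster correlation and cluster size, without covariate adjustment. The direction of the discrepancy is unknown. The choice of estimate, the confirmatory comparison and the type I error rate are not affected. It should be fixed, but it does not threaten the validity of the primary analysis.

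**What to change.** Restate the Sample Size section with the achieved number of intervention practices and the actual number of control group 1 practices. Give the power, or the detectable rate ratio, at that allocation. Keep the planning inputs for the rates, intracluster correlation and cluster size, and do not substitute observed results, since analysis has already begun. If credit is claimed for baseline adjustment, state the assumed share of variance explained.

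Replace the reference to about 3000 participating physicians in the abstract's Conclusions, and the matching reference in the Discussion, with 2460.

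Separately, confirm from the full protocol or analysis plan how practices with both participating and non-participating physicians are classified.

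The cost is two practice counts from the data holder, one recalculation and a few lines of text. No further enrolment is needed and the analysis model does not change.
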